# 3D Comparative Evaluation of Condylar Morphology Between Chronic Areca Nut Chewers and Nonchewers: Protocol for a Case-Control Study

**DOI:** 10.2196/84038

**Published:** 2026-03-06

**Keywords:** areca nut, cone beam computed tomography, CBCT, condyle, condylar morphology, temporomandibular joint

## Abstract

**Background:**

Areca nut (AN) is a commonly consumed psychoactive substance, especially in South and Southeast Asia. Chronic chewing of AN has been linked to multiple health problems, including temporomandibular joint (TMJ) disorders. Excessive strain on TMJ during chronic AN chewing can lead to repetitive injury, resulting in microtrauma and macrotrauma to both the TMJ and the surrounding masticatory structures. Previous studies have reported the long-term impact of AN chewing on TMJ by using conventional 2D imaging.

**Objective:**

This study aims to evaluate and compare condylar morphology in chronic AN chewers and nonchewers by using 3D imaging.

**Methods:**

This study will include 90 patients who will be divided into 2 groups: chronic AN chewers (n=45, 50%) and nonchewers (n=45, 50%). The study will be undertaken after obtaining institutional ethics committee approval and written informed consent from each patient. A detailed habit history of all the participants will be recorded. Each patient will undergo a clinical examination and radiographic evaluation of condylar morphology. Condylar morphology will be evaluated using cone beam computed tomography scans in both sagittal and coronal planes. All the findings will be recorded and then examined for statistical significance.

**Results:**

On comparison of condylar morphology between chronic AN chewers and nonchewers by using cone beam computed tomography, statistical variations relevant to structural and pathological alterations such as osteophytes, surface flattening, and erosions are likely to occur.

**Conclusions:**

This study aims to overcome the limitations of conventional 2D radiography and provide a more accurate assessment of condylar morphology. The findings should fill an existing gap in the literature by providing useful insights on the effects of chronic AN chewing on condylar structure by using 3D imaging. This research may help to improve the diagnosis, prevention, and management of TMJ disorders.

**Trial Registration:**

Clinical Trials Registry-India CTRI/2025/06/088238; https://ctri.nic.in/Clinicaltrials/pmaindet2.php?EncHid=MTMzNzQz&Enc=&userName=

**International Registered Report Identifier (IRRID):**

PRR1-10.2196/84038

## Introduction

Areca nut (AN) has a long history of use. A number of factors contribute to the popularity of AN chewing addiction, such as social acceptance, religious convictions, and perceived health advantages. AN is an ingredient in a variety of items, including *khaini*, *pan masala*, *mawa*, *paan*, and *gutkha*. AN (generally referred to as *Areca catechu* L and betel nut) is the fourth most frequently used psychoactive drug all over the world, after alcohol, nicotine, and caffeine [1].

AN is chewed for various reasons, such as pain treatment, euphoria, refreshment, and increased salivation. Although AN chewing is a highly common habit in Southeast Asia, its use has expanded to North America and Europe. The fruit of the *Catechu* tree produces AN as an endosperm. It is composed of tannins and alkaloids, which include arecoline, arecolidine, guvacine, guvacoline, and arecaidine. Regular consumption of AN may be harmful to one’s health. The risk of oral cancer increases with the frequency and duration of AN chewing, highlighting AN as a significant carcinogen. As a psychoactive substance, chronic AN use is categorized by the World Health Organization as a Group 1 human carcinogen, as regular AN chewing is associated with an increased risk of oral squamous cell carcinoma estimated at 2.3%-7.6%. The associated mortality risk is substantial, making this behavior clinically noteworthy [2,3].

Its principal alkaloid, arecoline, is responsible for systemic effects, including cardiovascular disturbances, metabolic disorders such as type II diabetes, immune dysregulation, neurotoxicity, respiratory impairment, and reproductive complications. An association between AN chewing and an increased risk of liver disease has been reported, with several studies demonstrating an additive effect on individuals who are positive for hepatitis B or C. Given its extensive adverse health consequences, AN use poses a significant public health concern [4,5].

Chronic chewing of AN, often kept in the mouth for hours, has been associated with various oral health problems. These include lesions of the mucosa, staining of teeth, dry mouth, periodontal diseases, and plasma cell stomatitis. Furthermore, it contributes to masticatory muscle pain and temporomandibular joint disorders (TMDs), which are common conditions affecting the craniofacial area. The overuse of the temporomandibular joint (TMJ) due to prolonged AN chewing is likely to cause microtrauma and macrotrauma to the TMJ and the masticatory apparatus [6].

Repetitive and prolonged chewing habits, such as AN, betel quid, and tobacco use, subject the masticatory muscles to sustained excessive forces, leading to masseter muscle hypertrophy, a benign condition characterized by an increase in the size of the masseter muscle, which may be unilateral or bilateral. With continued exposure, this mechanical overload results in increased muscle prominence and altered echogenicity of the masseter muscle on imaging [7,8].

Although there is some debate over its relationship with TMD, tooth wear is linked to cumulative parafunctional and oral functions. While modern studies show no clear relationship between tooth loss and TMJ changes, a correlation has been observed in Aboriginal and prehistoric populations. Some studies have claimed that parafunctional habits, including bruxism, clenching, and chewing gum or qat, may be linked to TMD [9].

One study examined the association between occlusal tooth wear and TMD by using the Smith and Knight Tooth Wear Index. Tooth wear was more common in patients with TMD, particularly grade 1 wear in the 26- to 40-year age group and in females, with posterior teeth most frequently affected. TMD is common in young adults and is significantly associated with functional and static occlusal parameters. These findings highlight the importance of evaluating occlusal factors for early diagnosis of TMD. On the basis of the TMD diagnostic criteria, previous studies have hypothesized that excessive tooth wear caused by chronic AN chewing is linked to TMD [9-11].

Mandibular condyle is a crucial bony structure that is often affected by TMD. It forms an articulation with the glenoid fossa, facilitating the movement of the mandible. The mandibular condyle is also the primary growth site in the development of the mandible. Normally, the condyle has a broadly ovoid form and measures approximately 8 mm to 10 mm anteroposteriorly and 15 mm to 20 mm mediolaterally. However, its morphology significantly fluctuates among different individuals and across different age groups. The shape and morphology of the condyle can change due to numerous factors such as normal developmental variability, developmental diseases, tooth wear, parafunctional habits, malocclusion, condylar remodeling, trauma, and disorders of the TMJ [12]. Tooth wear, regardless of its cause, disrupts the normal balance of force distribution, leading to structural adaptation within the condyle. These changes might not show any clear clinical symptoms [9].

A complete evaluation of structural changes in the condyle requires 2 steps: clinical examination and radiographic assessment to confirm the diagnostic findings. Orthopantomograms and transcranial views are some conventional radiographic techniques that have been used to examine the TMJ. However, these 2D images have limitations such as the superimposition of surrounding structures. In contrast, 3D imaging modalities, such as computed tomography (CT), magnetic resonance imaging (MRI), and cone beam CT (CBCT), offer a clearer view of condylar morphology, allowing a more accurate assessment of the TMJ [13].

CT imaging provides high-resolution, detailed images of bony structures. It effectively identifies bone abnormalities such as fractures, osteoarthritis, or degenerative changes in the TMJ. However, CT involves a high-exposure dose of ionizing radiation. It also has drawbacks in showing soft tissues, such as the articular disc, muscles, and ligaments, which are important for diagnosing TMD. Furthermore, CT can be expensive and may be impacted by artifacts from dental hardware, reducing image clarity [14].

MRI is a valuable tool for visualizing the TMJ, as it can produce clear images of soft connective tissues. However, MRI is not the best choice for checking bony abnormalities or fractures in the TMJ, as it is less effective for imaging bones compared to CBCT. Additionally, patients with metal implants, such as certain dental appliances or prostheses, may not be able to undergo an MRI due to dangers associated with the magnetic field [15].

CBCT is a reliable and effective imaging method for viewing craniofacial structures. This 3D imaging technique provides detailed structural information without overlapping or distortion. It is also preferred because it uses a relatively low radiation dose compared to conventional CT, making it safer for patients. Moreover, CBCT scans are more affordable than conventional CT scanners, making them a cost-effective choice for many dental and orthopedic practices. This combination of detailed imaging, safety, and efficiency makes CBCT an excellent tool for evaluating the shape of the condylar head [16,17].

Numerous studies have investigated the effect of chronic AN chewing and showed significant effects on oral tissues, including the oral mucosa and hard tissues [2]. However, a literature search revealed that few studies have focused on changes in condylar morphology among chronic AN chewers. Therefore, this study aims to use CBCT to compare the condylar morphological changes between chronic AN chewers and nonchewers, addressing the paucity of research on the condylar morphological changes associated with chronic AN chewers.

## Methods

A case-control study comprising 90 patients (chronic AN chewer: n=45, 50%) and nonchewer: n=45, 50%) will be conducted between September 2025 and May 2027.

### Ethical Considerations

The study will be carried out in Oral Medicine and Radiology department at Sharad Pawar Dental College and Hospital, after receiving approval from the "Institutional Ethics Committee (IEC)" of Datta Meghe Institute of Higher Education and Research (Deemed to be University), Sawangi (Meghe), Wardha, India [Approval No. DMIHER (DU)/IEC/2025/694)] and will be conducted in accordance with the Declaration of Helsinki. The patients, who are willing to participate and provide written informed consent will be included for the study. Participation is voluntary, and all participants may withdraw from the study at any time without any effect on their clinical care. All collected data will be fully de-identified prior to analysis and stored on password-protected, access-restricted institutional systems to ensure confidentiality and data security. No financial compensation will be provided to study participants. CBCT imaging in prospectively enrolled AN chewers will be performed only when clinically indicated and not solely for research purposes, in accordance with the ALARA (As Low As Reasonably Achievable) principle. No additional radiation exposure will be incurred for the control group, as their CBCT scans will be retrospectively analysed. All exposure parameters will be standardized and documented [18-20].

### Eligibility Criteria

#### Inclusion Criteria

Patients aged 18 to 40 years with a habit of chronic AN chewing for more than 1 year and a complete set of permanent dentition, excluding third molars, will be included in the study. Patients showing clinical evidence of generalized attrition and having a normal skeletal relationship will be considered for inclusion. Patients in the control group will have all permanent teeth except wisdom teeth, no history of AN chewing, and no evidence of attrition or reduced vertical height. Tooth wear will be assessed as a covariate by using the Smith and Knight Tooth Wear Index and will not be considered a criterion for group allocation [21].

#### Exclusion Criteria

Individuals who have undergone TMJ surgery or experienced a fracture, those with congenital TMJ anomalies, patients with a history of trauma from occlusion, those with systemic diseases affecting bone health, patients taking medications that impact bone health, and those with pathological lesions in the jaw or developmental tooth anomalies will be excluded.

### Study Procedure

The first step will be a detailed assessment of habit history. This will include chewing frequency per day, average duration of each chewing episode, total years of use, chewing-side preference, and type of AN product consumed. A cumulative “chewing-load index” will be calculated by combining frequency, daily duration, and total years of chewing to create a standardized measure of exposure. Additionally, an analysis of a subgroup within the AN chewer group will compare condylar morphology between the predominant chewing side and the nonchewing side. This will help to evaluate the mechanical effects related to each side. This method improves the measurement of exposure and boosts the study’s analytical power.

A complete medical history will also be gathered to rule out any systemic diseases affecting joints, medications influencing joint structure, and any history of trauma or surgery that impacts the TMJ.

A comprehensive clinical examination will be performed for each patient. The TMJ will be examined to identify any disorders. The assessment will include the following:

Joint movement inspection—evaluation of joint movement was done during mouth opening and closing to detect restricted mouth opening, pain, deviation, or deflection.Palpation—palpation of the joint will be performed to assess clicking sounds, crepitus, and tenderness during jaw movements.

Thorough intraoral examination will be done for patients with decreased vertical height due to AN chewing and loss of tooth structure. Tooth structure loss will be recorded based on the Smith and Knight Tooth Wear Index [22].

Each chronic AN chewer will then be evaluated for condylar morphology by performing CBCT. Imaging will be performed using a Planmeca ProMax 3D unit (Planmeca Oy; equipment ID: G-XR-109125), with the following parameters: 90 kV, 6.3 mA current, exposure time of 12.056 seconds, field of view of 5×5 cm, dose-area product of 447 mGy·cm², 251 slices, voxel size of 200 µm, rotation angle of 360°, pixel size of 200 µm, and software version 3.9.6.152. All AN nonchewers will be evaluated retrospectively, and their dental and medical history, clinical records, and radiographic data (CBCT) will be available.

Condylar morphology will be evaluated using CBCT scans in both sagittal and coronal planes. To calculate the length of the condyle, a line will be drawn connecting the anterior mandibular condyle point and the posterior mandibular condyle point. These points will be situated 4 mm below the superior mandibular condyle point on either side of the condyle [6]. Width of the condylar will be measured in the coronal plane as the linear distance between the medial and lateral mandible poles [6]. In contrast, height of the condyle will be determined as a perpendicular linear distance from the superior mandible condyle to a line drawn between the most inferior point of the sigmoid notch and the tangent of the posterior surface of the ramus in the sagittal plane [6], as shown in Figure 1.

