### Data Collection, Management, and Analysis

#### Plan of Data Collection

Patients who report to the Department of Oral Medicine and Radiology will have their AN chewing habit assessed. Following diagnosis, the patients will provide written informed consent and receive a comprehensive explanation of the intervention process. After consent has been obtained, CBCT will be used to analyze the AN chewer prospectively. This will create the following 2 distinct groups: AN chewers (45/90, 50%) and nonchewers (45/90, 50%), based on the patient’s habit history and comprehensive clinical examination. To improve transparency and reproducibility, the manuscript includes clearer and more organized reporting of the study design, participant recruitment, and flow. It also defines outcome measures. Additional details specify how CBCT imaging will be done, how clinical and habit-related data will be collected, and how all measurements will be recorded and analyzed. The procedures for radiologists, who were blinded to chewing status and attended calibration sessions, reliability testing, and statistical analysis, have also been described in more detail. This enhances methodological clarity and ensures that the study protocol is fully reproducible. All the results will be documented in a standardized tabular manner, as shown in Multimedia Appendix 2.

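### CBCT is limited to clinically indicated scans in one section, but other sections scan every chewer and eligibility requires no indication

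*Protocol article*

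**What the plan says.** All references are to the protocol article.

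- **Ethical Considerations** restricts scanning of the prospective group: "CBCT imaging in prospectively enrolled AN chewers will be performed only when clinically indicated and not solely for research purposes". It adds that controls incur no extra radiation because their scans are reviewed retrospectively.
- **Study Procedure** sets out habit history, medical history, TMJ examination and tooth-wear recording, and then states: "Each chronic AN chewer will then be evaluated for condylar morphology by performing CBCT".
- **Bias Mitigation** has all participants imaged by CBCT. Its allowance for what is possible most naturally concerns keeping the machine settings the same, not whether a scan is done.
- **Inclusion Criteria** for chewers begin "Patients aged 18 to 40 years with a habit of chronic AN chewing for more than 1 year" and go on to complete dentition apart from third molars, generalized attrition and a normal skeletal relationship. **Exclusion Criteria** cover TMJ surgery, fracture, congenital anomalies, trauma from occlusion, bone-affecting disease or drugs, jaw lesions and tooth anomalies. Neither list mentions an indication for CBCT.
- **Results** makes those two lists the only test of who is a study subject.
- **Plan of Data Collection** starts with "Patients who report to the Department of Oral Medicine and Radiology will have their AN chewing habit assessed", refers to a diagnosis that it does not specify, and continues "After consent has been obtained, CBCT will be used to analyze the AN chewer prospectively".
- **Objective** (Abstract) is unrestricted: "This study aims to evaluate and compare condylar morphology in chronic AN chewers and nonchewers by using 3D imaging".

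**The concern.** The restriction in Ethical Considerations is the article's stated radiation safeguard for the only group that is newly exposed. The procedural sections, followed literally, do not apply it. A site working from Study Procedure would scan an eligible chewer with no clinical reason for imaging, and that would be an exposure solely for research.

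Interpretation is at stake too. If the restriction governs, the chewers studied are those who needed CBCT. If the procedure governs, they are habitual chewers with attrition. The same between-group difference in condylar morphology would mean different things in those two populations, and the objective does not say which is intended. Controls enter through existing scans, whose indications may differ from those of the chewers. Scan indication is not among the scan details or the example adjustment factors listed in Bias Mitigation.

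**Working it through.** The article gives no figure to reproduce on this point, so the check is a comparison of its rules, applied to one case: a chewer who meets every inclusion criterion, meets no exclusion criterion, and has no clinical indication for CBCT.

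| Section | What it implies for this chewer |
|---|---|
| Inclusion and Exclusion Criteria | Eligible |
| Results | A study subject, since only the criteria decide |
| Study Procedure | Scanned |
| Bias Mitigation | Scanned |
| Ethical Considerations | Not scanned |
| Plan of Data Collection | Unclear: consent and CBCT follow an unspecified diagnosis |

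1. Both rules can hold together only if every enrolled chewer has an indication.
2. The criteria do not secure that. Age, duration of habit, dentition, attrition and skeletal relationship are not described anywhere as indications for CBCT.
3. The TMJ examination does not secure it either. It precedes the scan, but no imaging decision is attached to its findings, and the text proceeds to every chewer and not to those with findings.
4. Plan of Data Collection does not settle the matter. The diagnosis it mentions might be a clinical finding that justifies imaging, or simply the classification of the habit. It supports neither side.
5. The Abstract's methods statement, "Each patient will undergo a clinical examination and radiographic evaluation of condylar morphology", adds little. It covers both groups, and controls satisfy it with scans that already exist.

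The conflict therefore lies between Ethical Considerations on one side and Study Procedure with Bias Mitigation on the other, and the eligibility criteria leave it open.

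On size, the chewer group is planned at 45. The document gives no proportion of eligible chewers who would have an indication, so the number affected is unknown.

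**The case against.** The strongest reply is that Ethical Considerations contains the specific, restrictive rule, addressed to exactly these participants, while Study Procedure only describes the order of work. An explicit prohibition would ordinarily govern a general procedural sentence. On that reading a chewer without an indication is not scanned, does not count toward the 45 and is replaced by another. This is a reasonable reading and it may be the intended one. It defeats any claim that such a chewer cannot be handled at all, or must be either scanned in breach or kept without a primary outcome. It does not remove the mismatch, because no section states the precedence and the criteria still admit the chewer.

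A second reply is that this is a condensed article, and that how an indication is judged may be set out in the full protocol or the ethics submission. That holds for the mechanics of judging an indication. It does not cover two statements in the article itself that give opposite instructions.

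A reader might also take the recruitment text as proof that chewers are scanned on habit alone. Its reference to a diagnosis makes it too ambiguous for that. A reader might multiply the "dose-area product of 447" mGy·cm² per exposure by the group size to obtain a radiation total. Such a total would be only a ceiling for the whole group, and it would need the number of exposures per chewer, which is not stated. It says nothing about how many scans would lack an indication.

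**Conclusion.** The point holds as an inconsistency between stated rules that should be fixed before recruitment. Following Study Procedure or Bias Mitigation for an eligible chewer without an indication breaches the safeguard in Ethical Considerations, unless that section is assumed to override, and the article does not say that it does. The number of chewers affected is unknown.

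The conclusion rests on reading Bias Mitigation's qualifier as applying to machine settings, and on attrition or the chewing habit not being an indication in itself, which no section claims.

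A reader might infer that the chewer group will be enriched for condylar pathology, or that the sample will fall short. The documents support neither. The reasons for imaging are not given, and unscanned chewers can be replaced. What is established is that the target population is left open.

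**What to change.** Keep the restriction in Ethical Considerations and bring the other sections into line with it:

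1. Add to the chewer inclusion criteria: a documented clinical indication for CBCT. Do not require that the indication concern the joint. That would go beyond the present restriction and could select chewers for joint pathology relative to controls.
2. Make the scan statements in Study Procedure and Bias Mitigation subject to that indication.
3. Record the scan indication in both groups, from existing records for the retrospective controls, and report it by group.
4. State in the conclusions that the chewers are those with clinically indicated CBCT.

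The cost is a few changes of wording, one item on the data sheet and notification of the ethics committee. Results states that no participant had been recruited at submission. Accrual may be somewhat slower and the population narrower, but both already follow from the restriction as written. Recording the indication shows any selection by indication but does not remove it.
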